# Euthyroidectomy under local versus general anesthesia in health camp settings in Uganda: a protocol for randomized prospective equivalence single-blind controlled trial

**DOI:** 10.1186/s13063-023-07387-w

**Published:** 2023-05-31

**Keywords:** Euthyroidectomy, Local anesthesia, General anesthesia, Critical care, Africa

## Abstract

**Background:**

Endemic goiter is highly prevalent in Uganda at 60.2%, contributing to the high surgical burden. While compelling evidence suggest that in selected cases, thyroidectomy under local anesthesia (LA) is associated with fewer post-operative complications, low costs, and short hospital stays, local anesthesia is not considered a priority technique for thyroidectomy in resource-constrained settings such as Uganda, despite having fewer general anesthesia (GA) and critical care providers. The objective of this trial is to compare euthyroidectomy under local versus general anesthesia among patients with grade 1–2 uncomplicated euthyroid goiter in Uganda.

**Methods:**

This prospective equivalence randomized, single-blind controlled trial protocol will be conducted among eligible participants with grade 1–2 uncomplicated euthyroid goiters. The recruitment processes will start in October 2022 and end in April 2023. Consenting participants with an indication for thyroidectomy will be randomized into two arms of 29 participants in each arm during the Bulamu Health Care Organization surgical camps in Uganda.

**Discussion:**

The primary outcome of this trial protocol is to compare the early post-operative complications of euthyroidectomy done under LA versus GA. The outcome variables include post-operative pain based on visual analogue scale, nausea, vomiting, hematoma formation, and transient voice changes determined at an interval of 6, 12, and 24 h and at 30 days.

In addition, we shall compare the surgical site infection rates, procedure costs, hospital stay, and patients’ level of satisfaction based on a 5-point Likert scale and their willingness to undergo a similar surgery using the same anesthetic technique between the two groups. We hypothesize that euthyroidectomy under LA could potentially offer similar benefits as GA, reduce costs related to procedure, complications, and hospital stay while at the same time mitigating the unmet need for surgery attributable to shortage of general anesthesia providers and critical care facilities in low-income settings.

**Supplementary Information:**

The online version contains supplementary material available at 10.1186/s13063-023-07387-w.

## Introduction

Thyroid gland disorders are of global public health concern and are regarded the most common type of endocrine diseases after diabetes mellitus, accounting for 30–40% of glandular disorders [1]. Endemic goiter which is characterized by thyroid gland enlargement with or without affecting its function tops the list of thyroid gland disorders [2]. This problem disproportionately affects the poor. According to Qasim [3], there is a direct association between societal socioeconomic status, disease occurrence, and surgical outcomes that are dependent on medical care factors. As such, low-resourced countries have high prevalence of goiter, for instance up to 60.2% in Uganda [4], due to consumption of iodine-deficient meals or foods which interfere with iodine uptake. Furthermore, poorer individuals have impeded access to specialized health care and therefore present with advanced disease associated with compressive symptoms such as acute respiratory distress in addition to painful swallowing, hyperactivity of the gland (hyperthyroidism), and poor quality of life [4–6].

Thyroid surgery conventionally known as thyroidectomy is the principal treatment for symptomatic goiters that do not respond to medical treatment and remains among the most commonly performed surgical operations [6]. The operation is typically performed when the level of hormones from the gland which reflect its functionality has been normalized, hence the term euthyroidectomy.

Over time, various surgical approaches and anesthetic techniques have evolved to enable removal of a diseased thyroid gland. Historically, euthyroidectomy was associated with numerous post-operative complications that the first reported thyroid surgeon was jailed after the death of his patient in 1646 [7]. Albert Theodor Billroth was the first surgeon to popularize thyroid surgery, which encompassed primarily drainage of the thyroid cysts, although with concerns of post-operative pain and high levels of recurrence [7]. Subsequently, thyroidectomy was for years conventionally performed under regional local anesthesia (LA) resulting in loss of sensation and pain in a localized part of the body [8–10] with some series reporting favorable outcomes on over 20,000 patients as of 1990 [9, 11].

Following the advancement of general anesthesia (GA) techniques in which a state of unconsciousness is induced with complete absence of pain and reflexes, the number of thyroidectomies performed under GA increased and ultimately, GA became the preferred method under which thyroidectomy is carried out. In the current surgical practice, majority of surgeons prefer to perform thyroidectomy under GA which offers the advantage of pain-free surgery to the patient, thus reducing their anxiety and enabling a more relaxed operating room environment for the surgeon [8, 9].

Conversely, preference to GA is not without limitations. First, the longer recovery time from anesthesia results in prolonged hospitalization, delayed return to work, reduced patient turnover, and ultimately contributes to the unmet need for surgery. This culminates in patients presenting much later in life with huge goiters that have both local and systemic complications, compromising their general well-being, quality of life, and economic productivity. Secondly, in low-income settings with limited infrastructural and human resources, GA is comparatively undesirable due to concerns related to post-operative care and monitoring after the surgery such as lack of skilled staff and equipped intensive care units [6]. For instance, despite efforts from donor funding and south-west institutional collaborations, Uganda with its 45 million population boosts with only 100 qualified anesthesia providers (fewer than 0.05 anesthesia providers per 100,000 population) as opposed to high-income settings such as the UK with over 18 per 100,000 population [12]. Therefore, performing thyroidectomy under LA would offer the advantage of the anesthesia being administered by the surgeons themselves without putting much strain on the weak health systems.

Henceforth due to drawbacks of GA, in the last two decades, there has been an increase in the number of thyroidectomies performed under regional/LA combined with monitored anesthesia care [11, 13]. These numbers have even increased further with the development of minimally invasive thyroidectomy particularly in short-stay settings [9] and now, a few surgeons in the western world are currently doing thyroidectomies exclusively under LA [8].

Previous studies comparing euthyroidectomy under LA versus GA have shown mixed findings with regard to the benefits and post-operative outcomes. Other than overcoming the need to book for intensive care space and an anesthesiologist [14], which most patients in low-income countries cannot afford in the case of thyroidectomy under GA [15], LA has been associated with less post-operative pain, costs, hospital stay duration, post-operative nausea, vomiting, throat discomfort, and voice changes [9, 16, 17]. According to research in Nigeria [13], India [8], and USA [16], complications such as hematoma, surgical site infection, and colloid occur in less than 4% of cases of thyroidectomy performed under LA. In a randomized controlled study in Germany [9], the occurrences of post-operative complications (pain, nausea, vomiting, throat discomfort, painful swallowing, voice change, and difficulty in breathing were less in the group of patients who underwent thyroidectomy under LA as compared with those under GA in contrast to the prospective study in Uganda [18]. According to the USA [16] and Ugandan [18] studies, GA is also more associated with persistent hypothyroidism although the Kenyan cross-sectional review showed no difference[11].

In terms of cost, it has been arguably stated that performing thyroidectomy under LA might require additional training and capacity building in endocrine surgery which has cost implications, though comparatively similar costs would be incurred on supplies, critical care, and longer hospital stay [19, 20] more so in the error of COVID-19 where GA would increase in-patient risks. Cost of procedures is one of the limiting factors to access health care, and therefore, all measures should be taken to minimize the cost at which the surgical services are provided. A study done by Budhathoki et al. [20] in Nepal found out that the overall cost for thyroidectomy was less when done under LA as compared to when it is done under GA. The authors found that the cost of procedure included operation charge, material cost, medicines, and general ward bed charges. The mean cost in the participants that underwent thyroidectomy under GA was US $107.85 as compared to those under LA (US $65) [20]. Researchers Mamede and Raful in Brazil [19] found that the total cost of thyroidectomy was R$ 203.20 under GA compared to R$ 87.40 under LA. However, the significant difference in cost was only noticed in cost of treatment (drugs) with no significant statistical difference in the cost of hospital daily fees. In an Indian study by Shukla et al. [21], the mean cost incurred on patient from admission till discharge was Rs. 2189.32 for thyroidectomy under LA group versus Rs. 5520.00 in GA group. Such cost-effective studies are necessary in East Africa particularly in Uganda where there are budgetary constraints attached to health care, limited insurance coverage with most of the cost being paid out of pocket.

Further, in terms of patients’ level of satisfaction, which is a key patient-centered outcome, existing research in USA [16], Brazil [19], and Nepal [20] have shown no significant statistical difference in patients satisfaction for thyroidectomy done under LA versus GA and their participants would recommend to others to use either of the methods. In fact, a recent prospective comparative study in Nepal showed that the mean post-operative pain score using Likert scale was actually higher in LA versus GA group [20]. However, in East Africa where goiter is endemic, there have been no robust studies to compare the two anesthetic techniques in a randomized control setting. A Kenyan showed no difference between LA versus GA in terms of duration of surgery, operative complications, or length of facility stay [11]. Notably, the study had a smaller sample size of only 7 participants whose effect size could have limited the difference from being observed given the low incidence of such complications.

### Study rationale

According to Hisham and Aina [22], the prejudice to what technique works for the system resources is constrained by fear, doubt, and disbelief in the context of diverse cultures as to what constitutes safety, cost containment, and patient satisfaction. In addition, high level of evidence is pre-requisite to clinical application of research findings [23]. Recently, Schmidtke et al. have documented how lack of validation trials and complementary studies contribute to a huge gap between surgical research and clinical practice [23]. In this regard, until 19 March 2023, to the best of the authors’ knowledge, there are no systematic reviews and meta-analyses conducted to consolidate findings on this subject. Moreover, a majority of studies on the subject are observational and a paucity of randomized trials on the topic such as Snyder et al. [16], surgery was performed by a single surgeon with inter-operator reliability limiting the level of evidence to influence uptake into surgical practice. Validation randomized control studies are necessary to guide local medical practice particularly in low-income settings where there are competing priorities for resource allocation. To allow for local and regional comparisons, this study could inform the feasibility of using LA as a comparable alternative in the context of limited human and infrastructural resources in low-income Uganda. Most importantly, the findings will inform the applicability of either technique in surgical camp setting which is the most used avenue to address the unmet need for surgery in developing countries.

### Main objective

The aim of this randomized control trial is to compare euthyroidectomy under LA versus GA among patients with grade 1–2 goiter in Uganda.

### Specific objectives

The specific objectives of this study are as follows:To compare the occurrence rates of early 30-day post-operative complications (pain, hematoma, surgical site infection) following euthyroidectomy under LA versus GATo compare the cost implications of euthyroidectomy under LA versus GATo compare the patients’ level of satisfaction for euthyroidectomy under LA versus GA

#### *Hypothesis*

There is no difference in the early post-operative outcomes, cost, and patients’ satisfaction between euthyroidectomy performed under LA versus GA.

### Trial design

This study will be a prospective equivalence randomized single-blind controlled trial where the outcome data collectors will be blinded about the participants’ arms. The study is designed to be implemented in accordance with the SPIRIT guidelines for clinical trial protocols [24].

### Methods: participants, interventions, and outcomes

#### Study site and settings

The study will be conducted in camp settings of Bulamu Health Care Organization that are performed monthly in different regions of the country (Uganda).The Bulamu Healthcare is a well-established non-government (NGO) not-for-profit organization that was formed in 2016 as a branch of Bulamu Healthcare International. The Bulamu Super camp model is a uniquely cost-effective program that provides health care to impoverished families of rural Uganda. Bulamu plays the role of “Great Organizer” and brings the different government agencies and non-profit NGOs together in these camps and provide free services to Ugandans. Bulamu provides medical, surgical, obstetric, and gynecological care, public health, ophthalmology, dental care, and imaging services. The camp typically attracts over 15,000 patients in a week, approximately 3000 per day. In 2019, a total of 1433 surgeries were performed of which 53 (4%) were thyroidectomies. Over 150 to 400 surgeries are performed per week. Through the third quarter of 2019, the organization managed 49,449 patients. Both LA and GA resources are available in these camps. All operations are performed by senior consultant surgeons assisted by surgery residents. The recruitment shall be done within 4–5 camps (Figs. 1 and 2).

**Fig. 1 Fig1:**
[figure not shown]
Conceptual framework (outcomes)

**Fig. 2 Fig2:**
[figure not shown]
Participant timeline/study period

#### Study period

The study will be limited to a period from October 2022 to April 2023; thus, May 2023 will be the follow-up month for the last recruits.

### Eligibility criteria

#### Inclusion criteria of participants

Patients between 18 and 65 years with euthyroid goiter/or made euthyroid that will attend Bulamu Healthcare camps during the study period will be given equal chance to consent and participate in the study.

#### Exclusion criteria of participants

All patients with factors that have been previously documented to independently impact the outcome of thyroidectomy and are known indications for GA [13], including:Grade 3 goiter,Retrosternal goiter,Goiters with features of infiltration to surrounding tissues such as fixity underlying structures,Obesity,Previous neck surgeries, andDiabetes mellitus.

### Interventions: description/study procedure

Eligible participants based on our screening log will sign an informed consent document and undergo pre-anesthetic assessment 24 h prior surgery. This assessment will be undertaken in the designated tents used for our camp settings. All participants will be subjected to the Bulamu Healthcare fasting protocol of 6 and 2 h for solid and liquid diet respectively and will receive 1 g of intravenous ceftriaxone 60 min prior surgery. It is also a routine practice in Bulamu Healthcare to record all patients’ vital signs at 24 and 0 h prior surgery. These include but not limited to pulse rate, oxygen circulation, blood pressure, and ECG monitoring. All procedures are carried out under aseptic techniques. Following the procedure, all participants will receive intramuscular injection of diclofenac sodium 7 mg stat followed by 100 mg of oral diclofenac sodium 8 hourly for 5 days. Patients will be discharged home when they score at least 9 post anesthesia discharge scoring system [25] at the discretion of attending clinicians. Review at the 30th day will be in outpatient setting upon call by the outcome assessors. Telephone follow-up interview assessment option will be available for those who will reasonably be unable to attend an outpatient visit.

### Intervention

For group L (intervention group), as adopted from a study done by Aliyu et al. [13], infiltrative local anesthesia to achieve an anterior field block in this study will involve mixing of 0.5% bupivacaine, 2% lignocaine with 1:200,000 adrenaline.

The maximum dose of bupivacaine will be 3 mg/kg and the maximum dose of 2% lignocaine with 1:200,000 adrenaline will be 7 mg/kg [13].

The total calculated dose will be made up to 60 ml using water for injection or 0.9% normal saline; 20 ml of the mixture will be used for anterior field block which extends from the supra-sternal notch below to the cricoid cartilage above to the lateral borders of sternomastoid muscles.

Ten milliliters will be given along the incision line and another 10 ml under the investing layer of the pre tracheal fascia after raising sub-platysma muscle.

The remaining 20 ml will be given at 5 ml at each of the thyroid poles to minimize discomfort during mobilization.

Patients’ position and operative field preparation will be as in surgery under GA, but during draping, patient’s mouth and nose will remain exposed to allow continued communication and spontaneous breathing.

The communication will assure the surgeon of the safety of the recurrent laryngeal nerves.

The remaining operative steps will be carried out in accordance to the standard operative texts for thyroidectomy under GA [8, 13, 17]. In brief, the steps will include (a) positioning, painting, draping, (b) skin crease-incision and sub-platysma flap, (c) incision of investing layer of deep cervical fascia, retraction of strap muscles, and or division of middle thyroid vein, (d) superior pedicle handling, (e) recurrent laryngeal nerve and parathyroid gland safeguard, (f) thyroid gland identification and inferior thyroid vessel handling, (g) thyroid bed dissection, (h) repeat steps (f-g) on the contralateral side, (i) hemostasis with or without drain placement, and (j) wound closure.

For group G (control group), euthyroidectomy under GA will be as per the routine protocol described by Aliyu et al. [13]. Not to restrict a list of drugs that might be required in emergency situations during general anesthesia, the list is left open, and costs associated will be documented for each participant.

### Interventions: modifications

#### Adverse events and trial discontinuation for individual participants

The participants are anticipated to experience pain discomfort and or other complications due to the surgery as the main treatment for goiter not because of the study. In addition to breach of trial protocols, too much pain during surgery using LA will result in converting to GA (cross over) and advancing to stronger analgesics other than prescribed in protocol with ultimate discontinuation of individual participant from the trial.

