### Primary outcome measures

The primary outcome measures will be early 30-day post-operative complications (harms), including: pain, nausea, vomiting, hematoma, transient voice changes, and surgical site infection rates.

The complications will be reported verbally to nursing or to attending physicians for evaluation and recorded on a questionnaire in accordance with MedDRA® version 4.21 standardized reporting on medical and surgical procedures. The post-operative pain will be measured based on visual analogue scale of 0–10 where 0 means no pain and 10 means the worst possible pain. The pain will be assessed at an interval of 6, 12, and 24 h and at 30 days. The mean pain scores will be compared at using Student’s *t*-test, assuming normal distribution; otherwise, medians will be compared using non-parametric Kruskal–Wallis rank sum test.

The nausea and vomiting will be reported to nursing or attending physicians and recorded to the questionnaire using a nausea score on a scale of 0–9 where 0 means no symptom and 9 means very severe. The symptoms will be assessed at an interval of 6, 12, and 24 h and at 30 days. The mean nausea scores will be compared using a paired Student’s *t*-test, assuming normal distribution; otherwise, medians will be compared using non-parametric Kruskal–Wallis rank sum test.

Complications: hematoma, transient voice changes, and surgical site infection rates will be assessed at 6, 12, and 24 h and at 30 days will be reported in accordance with the Clavien Dindo classification of surgical complications [27], where grade I represents complications that do not require any additional intervention, grade II requires pharmacological treatment but not radiological or surgical intervention for instance blood transfusion, grade III requires radiological or surgical re-intervention, e.g., neck exploration and hematoma evacuation, grade IV representing life-threatening complications with at least one organ dysfunction such as respiratory failure that requires intensive care admission. The difference in proportions will be compared using Wilcoxon sum rank test.

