### Methods: data collection, management, and analysis

#### Data collection

Data will be collected by the PI and trained research assistants using a pre-designed and pre-tested structured questionnaire after educating participants for the need and significancy of follow up. The data collection tool was designed in English (the official language in Uganda) with translation in local language for the illiterate. A content validity index of 78% from 15 pre-test participants was considered adequate. Parts A and B of the questionnaire on socio-demographic and grade and size of goiter will be filled and completed. Part C of the questionnaire will be filled with intraoperative events. Part D of the questionnaire will be filled post-operatively and during follow up.

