### Data management and analysis

Data will be coded, entered in Excel version 2016, and later exported to STATA 14.2. for analysis. The intention-to-treat model will be used to minimize bias as way of reflecting what happens in real clinical practice. The intention-to-treat population will be used for inference and will be defined as all eligible randomized patients recruited in this study. Analysis will be done per study objective. Socio-demographic and surgical factors will be summarized descriptively using summary measures as proportions, means, medians, and measures of variation such as standard deviations for means, interquartile range for medians. All analyses will be computed at 95% confidence intervals and regarding *p* < 0.5 as statistically significant.

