### Missing data

Values will be imputed for participants with missing end points such as withdrawals, lost to follow-up, and crossovers. The baseline clinical and sociodemographic characteristics of participants in this category will be compared between the two groups.

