### Individual discontinuation

Other than breach of trial protocols due to non-adherence, too much pain during surgery using LA will result in converting to GA (cross over) and advancing to stronger analgesics in the post-operative period other than prescribed in protocol. This will result in ultimate discontinuation of individual participant from the trial.

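### Patients converted from local to general anesthesia are discontinued from the trial and imputed, so obtainable primary outcomes are lost despite the intention-to-treat claim

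*Protocol article*

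**What the plan says.** Four parts of the protocol article bear on this.

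- **Adverse events and trial discontinuation for individual participants:** "too much pain during surgery using LA will result in converting to GA (cross over) and advancing to stronger analgesics other than prescribed" in the protocol, "with ultimate discontinuation of individual participant from the trial". The same sentence also names breach of the trial protocol as a ground.
- **Individual discontinuation** repeats the rule: "This will result in ultimate discontinuation of individual participant from the trial".
- **Missing data:** "Values will be imputed for participants with missing end points such as withdrawals, lost to follow-up, and crossovers".
- **Data management and analysis:** "The intention-to-treat population will be used for inference and will be defined as all eligible randomized patients recruited in this study".

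On timing, Primary outcome measures says of pain that "The pain will be assessed at an interval of 6, 12, and 24 h and at 30 days"; nausea, vomiting, hematoma, voice change and wound infection follow the same schedule. Under Data collection, "Part C of the questionnaire will be filled with intraoperative events", so the conversion itself can be recorded.

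**The concern.** Intention-to-treat needs the outcomes of patients as randomized, whatever anesthetic they ended up with. Here a patient in whom LA fails is taken out of the trial during the operation, before any primary outcome has been measured, and a value is filled in later. The patient remains in the analysis set, but the data are not the patient's own.

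The pain-conversion trigger exists only in the LA arm and is tied to failure of the technique under test, so the missingness cannot be presumed ignorable. A later choice of imputation method cannot recover scores that were never taken. How patients fare after failed LA is also part of what a surgical camp choosing between the techniques needs to know, and the Study rationale gives feasibility and applicability in camps as the purpose of the trial.

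**Working it through.** **1. The rules side by side.** Conversion happens during surgery. The first primary assessment is at 6 h. Discontinuation is from the trial, stated twice, and crossovers are named as a class with missing end points. No section keeps converted patients in follow-up. Yet they are on site for the early assessments, and at day 30 the protocol offers a clinic visit, a telephone interview or a home visit. The Loss to follow-up section defines that status as being untraceable, which a converted patient is not. Their data are missing only because of the rule.

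**2. The plan's sample size.** Inputs from Sample size estimation: 83% (LA) and 79% (GA, general anesthesia) free of complications, margin 33 points, power 80%, type 1 error 0.05.

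n = [0.83×0.17 + 0.79×0.21] × (1.645 + 0.842)² / (0.33 − 0.04)² = 22.57, rounded up to 23; 23/0.9 = 25.6, rounded up to 26.

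The stated 26 per arm reproduces with a one-sided 0.05. The allowance is 26 − 23 = 3 per arm and is meant for loss to follow-up. Patients removed by rule would draw on the same 3.

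**3. Illustration of the effect on the equivalence conclusion.** The protocol gives no conversion rate (c), no event rate in converters (e) and no imputation method, so all three are assumed. The test is the any-complication comparison behind the sample size: 26 per arm, GA event rate 21%, equivalence declared when the 90% Wald interval lies inside ±33 points. The true LA rate is held at 21% + 33% = 54%, so the rate in non-converters is (0.54 − c×e)/(1 − c). For c = 10% and e = 100% this is (0.54 − 0.10)/0.90 = 48.9%.

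Simulated chance of falsely declaring equivalence (400,000 trials per setting). It is 4.6% when everyone is scored. With each converter's value drawn once at the observed rate of the remaining LA patients and then analysed as real data:

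| Converters with event | c = 5% | c = 10% | c = 20% |
|---|---|---|---|
| 100% | 7.6% | 12.0% | 26.1% |
| 70% | 6.0% | 7.5% | 11.8% |
| 54% | 5.2% | 5.7% | 7.1% |
| 30% | 4.2% | 3.7% | 2.8% |

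In the 54% row the converters do not differ from other LA patients, so there is no selection. That rise comes from treating single imputed values as observed. Drawing at the true rate of the remaining LA patients isolates selection: about 4.6% throughout that row, and 7.0%, 10.4% and 23.4% in the 100% row.

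If every converter is instead imputed as an event, the false-equivalence rate lies between 0.2% and 4.6%. The cost then falls on power. At the planned event rates (LA 17%, GA 21%), with 30% of converters truly having the event, power drops from about 80% with all scored to 76% at 10% conversion and 58% at 20%.

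**4. Pain score.** If k of 26 LA patients are imputed at the mean of the other LA patients, and their true mean differs from it by d, the LA mean is wrong by k/26 × d. For d between −2 and +2 points on the 0–10 scale:

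- k = 1: 1/26 × 2 = 0.08 either way
- k = 3: 3/26 × 2 = 0.23 either way
- k = 5: 5/26 × 2 = 0.38 either way

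**The case against.** The strongest reply is that the text does not explicitly stop outcome scoring. The rule sits under modifications to the intervention, where discontinuation often means leaving the allocated treatment, and the imputation sentence could be read as covering only those crossovers whose end points happen to be missing. That reading is possible but less natural: both statements say the patient leaves the trial, and crossovers are named as a class.

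A second reply is that the imputation method belongs in an analysis plan. That is true, and the unnamed method is not the point here. The discontinuation rule and the listing of crossovers are fixed in this document.

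Third, the size of the effect rests on assumptions, and part of the simulated inflation belongs to single imputation and not to the rule. This stands. The any-complication test is also not the analysis of separate complications described under Objective one.

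Fourth, conversions may be few, since difficult goiters, obesity and previous neck surgery are excluded and senior consultants operate. That is plausible, but the document gives no rate.

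Finally, the direction of bias is open. Converters receive GA and stronger analgesics, so their later scores may be higher than, equal to or lower than those of other LA patients. Breach of protocol could also remove GA patients.

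**Conclusion.** The concern holds. On the natural reading, the stated rules replace obtainable primary outcomes with imputed values for patients in whom LA failed, which contradicts the intention-to-treat claim. This conclusion rests on the text and needs no figure.

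Direction and size are unknown. Under the assumed settings, false equivalence moves from 4.6% to anywhere between 0.2% and 26.1%, depending on how many patients convert, how they fare and how they are imputed. The mean pain score in the LA arm shifts by at most 0.38 points with five converters and a 2-point difference. The conversion itself is not lost, only the outcome after it. The change should be made because the loss is avoidable and cannot be repaired at analysis.

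**What to change.** Amend three places.

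- **Adverse events and trial discontinuation for individual participants, and Individual discontinuation:** state that conversion to GA or rescue analgesia, in either arm, ends only the allocated technique. Assessments at 6, 12 and 24 h and at 30 days continue, and the observed outcomes are analysed in the assigned arm.
- **Missing data:** remove crossovers from the list. Withdrawals and losses to follow-up stay on it.

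Report conversions and rescue analgesia by arm. Whether to convert and which drugs to give remain clinical decisions.

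The cost is a short amendment and slightly more recording for converted patients. The assessments are already scheduled for everyone, so no patients or visits are added.
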